### 6.8 Exploratory endpoints

The samples that are collected to study exploratory endpoints are optional. The exploratory endpoints are differences between groups in

- CNS injury markers; Tau, NFL, SNE and S100B, after induction of anesthesia, 1-hour post- ECC and 24 hours post- ECC.
- NAG-excretion (U-NAG/U-creatinine) at time-points: after induction of anesthesia, at 1-hour after induction of ECC, at 1-hour post- ECC and 24 hours post- ECC.

### 6.9 Other pre-specified outcome measures

Post-operative bleeding measured as drain loss during first 24 h post operatively, need for transfusions, erythrocytes, plasma, thrombocytes, hemostatic pharmaceuticals, and platelet count, INR and APTT, post-operative lung and liver function as measured through need of respirator at 24 hours, time on ventilator and ALAT/ASAT, respectively.

### 6.10 Estimated sample size and power

A power analysis was performed using Fisher's test, based on including a population with a 50% risk of any AKI and a presumed reduction of any AKI in the test group to 35%, with 80% power and  $\alpha=0.05$ . This analysis resulted in a total population of 366 included patients.

## 7 Study Design

This is a prospective, multi center, double-blinded, randomized controlled clinical trial. The main outcomes will be reported as intention to treat. An as treated analysis will also be performed. This study design is chosen as the trial is considered to be of low risk to the participating patients, based on previous clinical investigations and as prospective randomized trials are considered state-of-the-art. The anticipated risk for participating patients is considered to be comparable in both treatment arms, therefore, the randomization does not lead to an additional burden for the patient. The study has been designed to involve as little pain, discomfort, fear and any other foreseeable risk as possible for the subjects. Patient safety is monitored continuously to identify potential unknown risk that would affect patient safety or alter the risk-benefit assessment in an unfavorable way.

## 7.1 Risks and Benefits

### 7.1.1 Anticipated clinical benefits

The document clinical benefit through use of the device PrimECC®, is increased oncotic pressure, improved fluid balance peri-operatively and reduced hemolysis during ECC, compared to when a crystalloid priming solution is used.

### 7.1.2 Anticipated adverse device effects

Dextran has been associated with rare anaphylactic reactions (<1 in 1000) such as urticaria, fever, chills, pruritus and anaphylaxis.

### 7.1.3 Risks associated with participation in the clinical investigation

Open cardiac surgery and use of ECC is a high-risk procedure. There are no known additional risks related to participation in this clinical trial. If anaphylaxis would occur, the patient is under strict surveillance at the time and the reaction could be treated.

### 7.1.4 Risk/benefit assessment

The low risk of anaphylaxis is reasonable considering the positive effect of improved fluid balance and reduced hemolysis compared to when a crystalloid solution is used to prime the ECC device. With the possible additional benefit of reduced AKI that will be investigated in this trial, the benefit side would be even further strengthened.

## 7.2 Study Groups

Patients enrolled according to the inclusion/exclusion criteria will, after written informed consent, be randomized to test group or control group. Randomization will be done through means of a randomization module.

An optimized allocation will be used based on;

eGFR  $\geq 60$ /eGFR  $< 60$

Expected ECC time  $\leq 60$  minutes/Expected ECC time  $> 60$  minutes

Both groups will receive medical care, based solely on clinical practice and their medical needs.

### 7.2.1 Blinding procedure

This is a double-blinded study. The only unblinded staff in the study is the perfusionist responsible for the randomization, priming of ECC machine, accountability of the investigational device (PrimECC®), and the dispensing record of the investigational device and comparator. The unblinded perfusionist should in their best effort, hide the identity of the priming solution used, for all the staff performing/attending the surgery and follow-up care.

Ideally the perfusionist running the ECC during surgery is unaware of the priming solution used and does not adjust perfusion or fluid therapy based on this.

Health care professionals involved in the surgery and follow-up standard of care should not be influenced to act and assess events on the knowledge of what kind of priming solution used.

### 7.2.2 Emergency unblinding

In case of an emergency where knowledge of the allocated priming solution is required the unblinded perfusionist is responsible for ensuring decoding of the subject.

The unblinded perfusionist is responsible for having the randomization result available for decoding at any time during the study period from Randomization until End of Study visit.

If unblinding is necessary, a Decoding Subject Form should be filled out with information of reason for decoding, description of event and safety event classification, if applicable. The form should be sent to the Sponsor within 24h.

## 7.3 Study Subjects

A total of 366 subjects aged  $\geq 18$  years, , that will undergo elective or urgent (non-emergency) cardiac procedure requiring the use of ECC, with an "Acute kidney injury risk score"  $\geq 30\%$  according to Birnie *et al* 2014, will be included after informed written consent. Subjects that require pre-operative dialysis, have known bleeding disorders, ongoing sepsis or endocarditis, known intolerance or contraindication to Dextran and patients undergoing emergency surgery will be excluded. Antithrombotic medication, except acetylsalicylic acid, should be discontinued before surgery according to the Institutions standard protocol.

### Inclusion criteria

- Has signed and dated the EC approved informed consent
- Subject is  $\geq 18$  years of age
- Requires elective or urgent (non-emergency) cardiac procedure requiring the use of ECC.
- Subject has a pre-operative "Acute Kidney Injury Risk Score"  $\geq 30\%$

[\*AKI score automatically calculated in eCRF CASTOR for eligible subjects.\*](#)

*Calculate eGFR (Cockcroft Gault Formula) which is used to calculate Acute Kidney Injury Risk Score at [https://qxmd.com/calculate/calculator\\_51/crcl-cockcroft-gault](https://qxmd.com/calculate/calculator_51/crcl-cockcroft-gault)*

### Exclusion criteria

- Unable to give informed consent
- Known bleeding disorder
- Has a known intolerance or contraindication to dextran
- Requires emergency cardiac procedure/surgery
- Currently using an antithrombotic medication which has not been discontinued per institution protocol
- Has ongoing sepsis or endocarditis
- Requires pre-operative dialysis
- The subject is considered by the Investigator to be unsuitable to participate in the investigation for any other reason.

## 7.4 Schedule of assessment

Table 1 Schedule of Assessment

|                                         | Pre-operative | After induction of anesthesia | 1 h ± 15 min after initiation of ECC | 1 h ± 15 min post-ECC | 24 ± 3h post- ECC | Postoperative day 2 (within 48h after ECC) | Postoperative day 3 (within 72h after ECC) | Postoperative day 4 (within 96h after ECC) |
|-----------------------------------------|---------------|-------------------------------|--------------------------------------|-----------------------|-------------------|--------------------------------------------|--------------------------------------------|--------------------------------------------|
| Informed Consent (up to 1 months)       | X             |                               |                                      |                       |                   |                                            |                                            |                                            |
| Assessment/ Evaluation                  | X             |                               |                                      |                       |                   |                                            |                                            |                                            |
| Medical history and demographics        | X             |                               |                                      |                       |                   |                                            |                                            |                                            |
| AKI score                   | X             |                               |                                      |                       |                   |                                            |                                            |                                            |
| Eligibility review          | X             |                               |                                      |                       |                   |                                            |                                            |                                            |
| Randomization                           | X             |                               |                                      |                       |                   |                                            |                                            |                                            |
| Hemoglobin                              | X             |                               |                                      |                       |                   |                                            |                                            |                                            |
| PFHb                                    |               | X                             | X                                    | X                     | X                 |                                            |                                            |                                            |
| ASAT, ALAT                              |               | X                             |                                      |                       | X                 |                                            |                                            |                                            |
| Serum creatinine            | X             | X                             |                                      | X                     | X                 | X                                          | X                                          | X                                          |
| Mechanical renal support                |               |                               |                                      |                       | X                 | X                                          | X                                          | X                                          |
| INR, APTT                               |               | X                             |                                      |                       | X                 |                                            |                                            |                                            |
| TNI/TNT                                 |               | X                             |                                      | X                     | X                 |                                            |                                            |                                            |
| U-NAG  , U-Crea, U-Alb      |               | X                             | X                                    | X                     | X                 |                                            |                                            |                                            |
| Tau and NFL, NSE and S100B  |               | X                             |                                      | X                     | X                 |                                            |                                            |                                            |
| Fibrinogen                              |               | X                             |                                      |                       | X                 |                                            |                                            |                                            |
| Blood gas                               |               | X                             | X                                    | X                     | X                 |                                            |                                            |                                            |
| Platelet count                          |               | X                             |                                      |                       | X                 |                                            |                                            |                                            |
| Fluid balance                           |               | X                             |                                      |                       | X                 |                                            |                                            |                                            |
| Transfusion                             |               | X                             |                                      |                       | X                 | X                                          | X                                          | X                                          |
| AE/SAE                      |               | X                             | X                                    | X                     | X                 | X                                          | X                                          | X                                          |

 Pre-operative, one day before planned surgery. Surgery postponed ≥ 7days, recalculation of AKI score required.

 Pre-operative, one day before planned surgery.

 Surgery postponed ≥ 7days, a new s-crea required.

 Collection of urine samples for analysis of U-NAG is optional.

 Collection of plasma and serum samples for analysis of CNS injury markers is optional.

 Evaluation of new AE/SAE until Postoperative day 4. Ongoing AE/SAE will be followed-up until discharge from hospital.

## 7.5 Timeline

It is expected that the study will be performed Q1 2020 to Q2 2024. The subject follow-up period is 96 h after ECC, and the study will be considered completed at 96 hours after ECC of the last included subject.

## 8 Schedule of Assessments

A preliminary review of medical records should be performed to assess if a subject will be eligible for participation in the study. This includes medical history, renal status, liver status, heart and lung status and any infectious diagnosis. Investigators or delegated staff are responsible for obtaining informed consent and authorization to use and disclose protected health information before randomization. The study does not require specific screening study procedures other than a medical chart review. A final review of the subject's medications and medical history will be confirmed at time of surgery to make sure that nothing has changed since consenting to the study. The "Acute Kidney injury risk score" will be used to evaluate that the subject fulfil the inclusion criteria at admission the day before surgery. If, for any reason, the surgery is postponed  $\geq 7$  days, a recalculation of AKI score is required with a retaken sample of s-crea.

### 8.1 Informed Consent

Subjects who are eligible for inclusion will be given written and oral information in advance to allow for time to consider participation\*. All subjects participating shall give consent prior to any study activity. A copy of the signed and dated consent shall be provided to the subject.

*\*Note, only applies in Norway: The investigator or his/her authorized designee obtaining the Informed consent should not be the same that performs the surgical procedure in order to avoid any coercion or undue improper influence on, or inducement of, the subject to participate.*

### 8.2 Prior to surgery

When a subject who meets eligibility criteria and consents to participate, the center will perform randomization. Subject data, i.e., gender, age, BMI, height, weight, presence of diabetes, kidney function, heart function (LVEF; most recent assessment pre-operative), liver function, hypertension (pharmaceutical treatment or  $> 140/90$  mmHg), smoking history, self-reported ethnicity, Euroscore (optional) and medication is registered as well as type of planned procedure.

### 8.3 After induction of anesthesia

When the arterial line is set and the subject is anesthetized blood is drawn and analyzed for serum-creatinine, Pfhb, ASAT, ALAT, Tau, NFL, NSE, S100B, fibrinogen, platelets, APTT, INR, TNI/TNT and blood gases. *Collection of plasma and serum for analysis of Tau, NFL, NSE, and S100B is optional.*

A urine sample is taken and analyzed for U-NAG (*U-NAG analysis is optional*), U-creatinine and U-Alb.

### 8.4 1- hour after induction of ECC

At 1 hour  $\pm 15$  minutes after induction of ECC a urine sample is collected to analyze U-NAG (*U-NAG analysis is optional*), U-Crea and U-Alb. And a blood sample is drawn from arterial line to analyze for Pfhb and blood gases.

### 8.5 1-hour post-ECC

At 1 hour  $\pm 15$  minutes post- ECC a urine sample is collected to analyze for U-NAG (*U-NAG analysis is optional*), U-Crea, U-Alb and blood is drawn to analyze serum-creatinine, Pfhb, Tau, NFL, NSE, S100B,

TNI/TNT and blood gases. *Collection of plasma and serum for analysis of Tau, NFL, NSE, and S100B is optional.*

## 8.6 24 hours post -ECC

At 24±3 hours post ECC, a urine sample is collected to analyze for U-NAG (*U-NAG analysis is optional*), U-Crea and U-Alb and blood is drawn to analyze serum-creatinine, PfHb, ASAT, ALAT, Tau, NFL, SNE, S100B, fibrinogen, platelet count, APTT, INR, TNI/TNT and blood gases. *Collection of plasma and serum for analysis of Tau, NFL, NSE, and S100B is optional.*

## 8.7 Postoperative day 2 (within 48 h after ECC)

Within 48 hours after ECC, blood is drawn to analyze serum-creatinine.

## 8.8 Postoperative day 3 (within 72 h after ECC)

Within 72 hours after ECC, blood is drawn to analyze serum-creatinine.

## 8.9 Postoperative day 4 (within 96 h after ECC)

Within 96 hours after ECC, blood is drawn to analyze serum-creatinine.

## 8.10 Intraoperative parameters

Intraoperative parameters comprising anesthesia start time, ECC time, aortic cross-clamp time, surgery time from start of incision until closure of incision and ventilator time are registered. The subject fluid balance, including all infusions of crystalloids and colloids, transfusions, bleeding and urine output are registered.

## 8.11 Postoperative parameters

In addition to the laboratory analysis defined above, the patient fluid balance is registered as the sum of infusion of crystalloids, colloids, transfusions, bleeding and urine output. All infusions of blood and/or plasma products are recorded during the study period. Reoperation for bleeding, time on ventilator, significant infections, and ICU length of stay and hospital length of stay are registered.

Use of mechanical renal support such as continuous renal replacement therapy (CRRT) or hemodialysis is registered during the study period.

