## 6 Study Hypotheses and Objectives

### 6.1 Hypothesis

The main hypothesis is that, in a population at high risk for postoperative AKI, priming the ECC circuit with PrimeECC® instead of only crystalloid solution will lead to a reduced rate of postoperative AKI.

The secondary hypothesis is that priming of the ECC circuit with PrimeECC®, compared to a crystalloid solution, will lead to less tubular cell injury, less hemolysis, better fluid balance and better organ preservation.

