### 11.4 Analysis of secondary objective

The secondary objective of this study is to test if use of the new priming solution reduces the levels of hemolysis and or alleviate the reduction of eGFR commonly associated with the surgical procedure, compared to when a non-colloid priming solution is used. These repeated continuous variables will be analyzed using mixed models for repeated measures (MMRM) adjusted for baseline on both FAS population and PP-population.

Other secondary objectives include to define safety variables in terms of bleeding, coagulation, pulmonary, cardiac and liver function and to assess fluid balance.

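### Section 8.11 registers postoperative fluid balance as a sum that adds bleeding and urine output to the fluids given; read literally, this is turnover and not net balance

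*Protocol*

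**What the plan says.** Section 8.11 gives the postoperative rule: "the patient fluid balance is registered as the sum of infusion of crystalloids, colloids, transfusions, bleeding and urine output". Section 8.10 covers the operation itself and names the same components, with no formula and no summation: "The subject fluid balance, including all infusions of crystalloids and colloids, transfusions, bleeding and urine output are registered". Table 1 marks fluid balance after induction of anesthesia and at 24 ± 3 h post-ECC.

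The variable has a role in the trial's claims. The secondary hypothesis in Section 6.1 is that the test prime "will lead to less tubular cell injury, less hemolysis, better fluid balance and better organ preservation". Section 11.4 ends its list of other secondary objectives with "pulmonary, cardiac and liver function and to assess fluid balance". Section 7.1.1 says that the clinical benefit of the device "is increased oncotic pressure, improved fluid balance peri-operatively and reduced hemolysis during ECC". Fluid balance is not among the endpoints and outcome measures listed in Sections 6.5, 6.6, 6.8 and 6.9.

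**The concern.** A fluid balance is what goes in minus what comes out. Section 8.11 is the only place in the protocol that says how the components are combined, and it combines them all with the same sign. A patient who passes more urine for the same intake would then have a larger recorded value, although the net balance is smaller.

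The sentence also describes what sites register. If the postoperative form followed it and held a single total, different sites could resolve the sign differently and the net value could not be rebuilt afterwards. The Table 1 window spans the periods of both 8.10 and 8.11, so a cumulative balance needs one rule across the two. At stake is the fluid-balance part of the secondary hypothesis.

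**Working it through.** The protocol states no fluid-balance figure, so there is none to reproduce. The check compares the literal rule with a net balance.

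**Inputs.** From Section 8.11, for each patient:
- I = crystalloids + colloids + transfusions (intake)
- O = bleeding + urine output (output)

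**Per patient.**
- Literal rule: S = I + O
- Net balance: N = I − O
- Excess of the literal rule: S − N = 2 × O

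**Between groups.** Let dI and dO be the test-minus-control differences in mean intake and mean output.
- Literal rule: dS = dI + dO
- Net balance: dN = dI − dO
- Distortion: dS − dN = 2 × dO, which is zero when dO = 0
- The two have opposite signs when (dI + dO)(dI − dO) = dI² − dO² is negative, that is, when |dO| > |dI|

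**Illustrations.** All volumes below are assumptions in ml, because the protocol gives none. Each pair is intake / output.

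| Case | Test | Control | dI | dO | Net: test, control, difference | Literal sum: test, control, difference |
|---|---|---|---|---|---|---|
| 1. Equal outputs | 2500 / 1500 | 3000 / 1500 | −500 | 0 | 1000, 1500, −500 | 4000, 4500, −500 |
| 2. Output difference smaller than intake difference, opposite direction | 3000 / 3000 | 4000 / 2500 | −1000 | +500 | 0, 1500, −1500 | 6000, 6500, −500 |
| 3. Output difference equal to intake difference, same direction | 3000 / 2000 | 4000 / 3000 | −1000 | −1000 | 1000, 1000, 0 | 5000, 7000, −2000 |
| 4. Output difference larger than intake difference | 2500 / 1800 | 3000 / 1000 | −500 | +800 | 700, 2000, −1300 | 4300, 4000, +300 |
| 5. Equal intakes | 3000 / 1800 | 3000 / 1300 | 0 | +500 | 1200, 1700, −500 | 4800, 4300, +500 |

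Case 1 shows no harm to the comparison, although each patient's value is too high by 2 × 1500 = 3000 ml. Case 2 shrinks a real difference. Case 3 shows a difference where there is none. Cases 4 and 5 reverse the sign, and in both |dO| exceeds |dI|.

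**The case against.** The strongest reply is that this is loose drafting. Bleeding and urine output are plainly losses, the quantity is called a balance, and the protocol speaks of it as something that improves, which does not fit turnover. On that view the word means a signed sum. This is plausible and may well be the intention, but no section says so, and a multicentre trial should not leave each site to infer it.

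A second reply is that formulas for derived variables usually sit in the SAP, which is not shown. That holds for a formula left open. Here the protocol states one, in a sentence about what is recorded. A SAP can correct it only if the components are stored.

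A third reply is that the components are available. Section 8.10 has them registered during the operation, Section 8.11 separately records blood and plasma products, and Section 6.9 measures drain loss over the first 24 h. Much of this stands. What no section clearly requires is that postoperative crystalloid, colloid and urine volumes be held as separate values, and the eCRF is not shown.

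A reader might go further and infer that the rule will reverse the hypothesised benefit. The documents do not support that. Reversal needs |dO| > |dI|. The earlier randomized trial of 39 + 41 patients is reported (Sections 2 and 4) as showing less intravenous fluid with the test prime and no significant difference in bleeding, and no urine difference is reported. Equal outputs cannot be presumed either, so distortion is possible but its size is unknown.

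A reader might also infer that the trial cannot answer its fluid-balance question, or that Section 8.10 contains the same error. The first holds only if a single unsigned postoperative total is all that is kept. The second is not so, because 8.10 only lists components.

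**Conclusion.** Wrong as written, minor. Taken literally, Section 8.11 overstates each patient's net balance by 2 × (bleeding + urine output) and shifts the between-group difference by twice the difference in mean output. The shift is nil with equal outputs, and the sign is wrong only when the output difference exceeds the intake difference in absolute size.

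The conclusion rests on the plain meaning of the sentence and on the absence of any other rule in the protocol. The illustrative volumes are assumed and carry no weight as a forecast. The consequence is confined to one component of the secondary hypothesis and one of the other secondary objectives. The primary endpoint, its test and the sample size do not use fluid balance.

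**What to change.** Replace the wording in Section 8.11 with: fluid balance = (crystalloids + colloids + transfusions) minus (bleeding + urine output). Record each postoperative component separately in the eCRF, as Section 8.10 already provides for the intraoperative period, and derive the balance centrally over the Table 1 window, from induction of anesthesia to 24 ± 3 h post-ECC.

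Nothing more is needed for this defect. A term for prime volume would correct nothing identified here, since Section 5.3 requires the same volume in both arms. Whether fluid balance should be listed as an outcome in Section 6.6 or 6.9 is a separate decision about endpoints.

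The cost is one sentence, one derived variable and a check that the eCRF holds the postoperative components separately. If it already does, no further data collection is involved. If it holds only a total, the form needs the component fields added.
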